### Recruitment

Participants will be patients diagnosed with T1DM, T2DM, and/or post-transplant DM if they initiate basal insulin or intensify their insulin regimen to a basal-bolus regimen at the tertiary hospitals Samsung Medical Center or Samsung Changwon Hospital in Korea. Individuals who are willing to participate in the clinical trial and who meet the inclusion criteria will receive written information about the study and must provide informed consent, as approved by the ethics committee [Additional file 1].

### Outcome variables

The primary outcome will be the proportion of patients who reach the optimal insulin dose within 12 weeks of enrolling in the study, without severe hypoglycemia or unscheduled visits to the clinic. Achievement of the optimal insulin dose is defined as follows: A. For a patient who uses basal insulin only or basal insulin with pre-meal rapid-acting insulin once per day, 1) three or more fasting blood glucose values within the target range (80 to 130 mg/dL or 100 to 140 mg/dL) during week 12 (last 7 days prior to visit 3), 2) no nocturnal (from 11 pm to 7 am) or pre-breakfast hypoglycemia (<70 mg/dL) during week 12, and 3) variation of basal insulin dose (defined as the difference between the highest and lowest basal insulin doses) <10% of the mean total basal insulin dose during week 12. B. For a patient who uses multiple daily injections, including basal insulin with pre-meal rapid-acting insulin at least twice per day, the criteria are those in A plus 4) three or more days in which the correction dose of pre-meal insulin is required less than three times per day during week 12, and 5) no daytime (from 7 am to 11 pm) hypoglycemia (<70 mg/dL) during week 12.

The secondary outcome will be the proportion of patients who reach HbA1c <7% without severe hypoglycemia (unrecoverable hypoglycemia without the help of others) at weeks 12 and 24. Other secondary outcomes include mean fasting blood glucose values for three consecutive days prior to weeks 12 and 24; levels of HbA1c at weeks 12 and 24; the proportion of patients having hypoglycemia (total, asymptomatic, daytime, nighttime, severe hypoglycemia, and coma/convulsions) at weeks 12 and 24; the number of steps taken during weeks 1–12 and weeks 13–24; recorded exchange unit by food group (grain, fish, vegetable, fat, milk, and fruit groups) in each breakfast, lunch, and dinner on 3-day food diary at weeks 12 and 24; daily insulin dose, body weight, and blood pressure at weeks 12 and 24; lipid profiles including total cholesterol, high-density lipoprotein (HDL) cholesterol, triglycerides, and low-density lipoprotein (LDL) cholesterol at weeks 12 and 24; body composition, including lean body mass and fat mass, at weeks 12 and 24; satisfaction evaluation by Diabetes Treatment Satisfaction Questionnaire (DTSQ) [13–16] and a questionnaire for ICT-based centralized clinical trial monitoring at weeks 12 and 24; the number of self-monitoring blood glucose measurements; the mean duration of medical consultations by doctors at the outpatient clinic; and the number and mean duration of telephone counselling by diabetes educators at weeks 12 and 24.

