## Methods

### Hypotheses

Our primary hypothesis is that the ICT-based intervention group will produce a greater proportion of patients who reach optimal insulin dose within 12 weeks compared with the conventional intervention group. Our secondary hypothesis is that the ICT-based intervention group will have a greater proportion of patients who reach HbA1c <7% without severe hypoglycemia at weeks 12 and 24, improved glycometabolic control (including levels of fasting glucose, HbA1c, lipid parameters, body weight, lean body mass, fat mass, and blood pressure), step count, exchange units for each food category, and fewer hypoglycemic events or acute complications relative to the conventional intervention group.

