### Sample size assumptions

In a previous study that utilized mobile phones for insulin titration intervention for subjects with type 2 diabetes, proportions of patients reaching optimal insulin dose within 12 weeks were 88% and 37% in the intervention and usual care arms, respectively [7]. In the present clinical trial, for both the intervention and control groups, we provide telephone counseling 1 week after patient education and allow telephone counseling if the blood glucose level does not meet the target level in both ICT-based intervention and conventional intervention groups. Therefore, the rate of reaching the primary endpoint of the control group is expected to be 55%, higher than that of the reference, and the estimated proportion of the intervention group that meets optimal insulin dose is 88%, which is similar to the reference. With these assumptions, a sample size of 38 subjects per group is needed with a two-sided alpha threshold of 0.05 with 90% power. We aimed to recruit 96 participants (48 per group) to allow for a dropout rate of 20% during follow-up (Samsung Medical Center, *n* = 76; Samsung Changwon Hospital, *n* = 20) [17].

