### Telephone counseling and re-introduction of intervention

At week 1, educators provide telephone counseling to all subjects to assess concomitant medication use or any adverse events and to re-instruct insulin dose adjustment and PHR apps. Subjects who are screening failures must return the at-home measurement device to the clinic. All participants are instructed to call the diabetes educator if the measured blood glucose level is <70 mg/dL more than once, or if the blood glucose level is not in the range of the glycemic target more than twice. Also, unscheduled visits to the clinic are available if a subject has one or more severe incidents of hypoglycemia (requiring other help for recovery) during the study period, hypoglycemia (<70 mg/dL) two or more times per week, or experiences fasting blood glucose >200 mg/dL three or more times in the morning and wants to see a doctor during weeks 1–12. Unscheduled visits to the clinic are also allowed for subjects who have difficulty in insulin dose adjustment, despite two or more unscheduled tele-visits. All subjects will record a 3-day food diary regarding the exchange unit for each nutrient group (e.g., grain, fish, vegetable, fat, milk, and fruit groups) in the breakfast, lunch, and dinner prior to visits 3 and 4.

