### Evaluation of hypoglycemia

Hypoglycemia is defined using the following criteria: 1) asymptomatic hypoglycemia (if blood glucose is measured as <70 mg/dL without clinical symptoms); 2) symptomatic hypoglycemia (the symptoms of hypoglycemia (e.g., sweating, severe hunger, shivering, and panic) including blood glucose level < 70 mg/dL or not confirmed); 3) daytime hypoglycemia (7 am-11 pm; hypoglycemia before sleep after the wake-up); 4) nocturnal hypoglycemia (11 pm-7 am; hypoglycemia from sleep to wake-up); 5) severe hypoglycemia (help is needed to restore glucose level). If subjects have hypoglycemia meeting the above criteria, they use the hypoglycemia diary in the PHR app to record the details of the hypoglycemic event. At each clinic visit at weeks 12 and 24, the incidence and type of hypoglycemia are identified and recorded via face-to-face interview.

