### Evaluation of the stability of ICT-based centralized clinical trial monitoring

At week 12 and 24 clinic visits, the CRC will identify the frequency of hypoglycemia, insulin dose, body weight, and blood pressure in the face-to-face interview; analyze the consistency of the data examined by the CRC and transmitted data from the PHR app, including the hypoglycemia diary; and verify the efficacy of the ICT-based centralized clinical trial monitoring. The satisfaction questionnaire about the DTSQ and ICT-based centralized clinical trial monitoring will be evaluated.

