### Data analysis

All continuous variables will be presented as mean ± standard deviation, and categorical variables will be presented as frequency and proportion. For analyzing primary outcomes, the percentage of patients who reached the optimal insulin dose within 12 weeks is presented, and the difference between the two groups is compared using Pearson’s chi-square test or Fisher’s exact test if the frequency is low (<5). Differences are analyzed using Pearson’s chi-square test or Fisher’s exact test for categorical variables and Student’s t-test or Wilcoxon’s rank-sum test for continuous variables of secondary outcome variables. Comparisons between the two groups will be performed using a stratification analysis based on the use of pre-prandial insulin two or more times per day and each research institute. Prespecified subgroup analyses, including use of immunosuppressants (including steroids); type of DM; HbA1c >9%; use of pre-prandial insulin; aged over 65, 60, or 55; type of basal insulin; and stage of chronic kidney disease at baseline are performed. For handling missing data, last-observation-carried-forward (LOCF) imputation method would be performed.

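### The secondary hypothesis is fewer hypoglycemic events, but the listed comparison is only the proportion of patients affected; an event rate should be added beside it

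*Protocol article*

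**What the plan says.** In the protocol article, the section Hypotheses includes, within the secondary hypothesis, "fewer hypoglycemic events or acute complications relative to the conventional intervention group".

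Outcome variables lists hypoglycemia among the other secondary outcomes as "the proportion of patients having hypoglycemia (total, asymptomatic, daytime, nighttime, severe hypoglycemia, and coma/convulsions) at weeks 12 and 24". No count or rate of events is listed, although the same list does use counts for steps, self-measurements of glucose and telephone counselling.

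Data analysis states: "Differences are analyzed using Pearson’s chi-square test or Fisher’s exact test for categorical variables". Continuous secondary outcomes get a t-test or rank-sum test. No count or rate model is named.

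Three other sections bear on the point.
- Evaluation of hypoglycemia uses a low threshold that needs no symptoms: "asymptomatic hypoglycemia (if blood glucose is measured as <70 mg/dL without clinical symptoms". It also admits symptomatic events without a confirming glucose value.
- Telephone counseling and re-introduction of intervention foresees repeat events, since one ground for an unscheduled visit is "hypoglycemia (<70 mg/dL) two or more times per week".
- Evaluation of the stability of ICT-based centralized clinical trial monitoring has event frequency recorded at weeks 12 and 24: "the CRC will identify the frequency of hypoglycemia, insulin dose, body weight, and blood pressure in the face-to-face interview". It is used there to check consistency with the app data, not to compare the arms.

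**The concern.** The hypothesis is about how many events occur, and the listed outcome is about how many patients have any. The two agree closely when events are rare and separate as patients begin to have repeat events. The intervention could cut the number of events in patients who still have at least one, and the listed comparison would not register it.

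Safety of dose adjustment is part of the trial's stated aim. If the proportions turn out similar, the report could conclude that hypoglycemia did not differ while event rates did. This is not just detail left to an analysis plan: the article itself states hypothesis, outcome and test, and the first does not match the other two.

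**Working it through.** **The plan's own figure.** For the primary outcome the protocol states "a sample size of 38 subjects per group is needed with a two-sided alpha threshold of 0.05 with 90% power", assuming 55% and 88%. With pooled proportion (0.55 + 0.88)/2 = 0.715:

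n = [1.960·√(2·0.715·0.285) + 1.282·√(0.55·0.45 + 0.88·0.12)]² / 0.33² = 37.2, so 38 per arm. Allowing 20% dropout, 38/0.80 = 47.5, so 48. Both figures reproduce. The protocol gives no corresponding figure for hypoglycemia.

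**Inputs for the check.** From the protocol: 38 per arm, two-sided alpha 0.05. Assumed, because the documents give no value: control mean events per patient μ over the window, rate ratio 0.6, and negative binomial dispersion k (k = 0 is Poisson).

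**Formulas.**
- Patients with any event: P = 1 − (1 + kμ)^(−1/k), or 1 − e^(−μ) for Poisson. Power is that of the Pearson chi-square test on the two proportions, by exact enumeration.
- Rate comparison: var(log RR) = (1/μ₀ + 1/μ₁ + 2k)/n, with power Φ(|log 0.6|/SE − 1.96).

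**Worked case, k = 1, μ₀ = 3.6 (0.3 per week for 12 weeks).** μ₁ = 0.6 × 3.6 = 2.16. Any event: 1 − 1/4.6 = 78% against 1 − 1/3.16 = 68%; chi-square power 17%. Rate: (0.278 + 0.463 + 2)/38 = 0.0721, SE 0.269, 0.511/0.269 = 1.90, power Φ(−0.06) = 48%.

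| k | Control mean | Patients affected | Power, proportion | Power, rate |
|---|---|---|---|---|
| 0 | 0.1 | 9.5% v 5.8% | 10% | 9% |
| 0 | 1 | 63% v 45% | 36% | 49% |
| 0 | 3 | 95% v 84% | 40% | 92% |
| 0 | 6 | 99.8% v 97% | 2% | 99.7% |
| 1 | 0.1 | 9% v 6% | 9% | 9% |
| 1 | 0.3 | 23% v 15% | 14% | 16% |
| 1 | 1 | 50% v 38% | 19% | 31% |
| 1 | 3.6 | 78% v 68% | 17% | 48% |
| 1 | 12 | 92% v 88% | 11% | 56% |
| 2 | 3.6 | 65% v 57% | 11% | 30% |
| 2 | 12 | 80% v 75% | 9% | 34% |

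**Where the loss begins.** For k = 1, the share of the information on the log rate that the yes/no outcome keeps is 1/(1 + μ): 77% at 0.3, 50% at 1 and 22% at 3.6. The half-way point is a mean of about 1.26 for Poisson, 1.0 for k = 1 and 0.81 for k = 2.

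**The case against.** The strongest reply is that the size of the problem rests on an event rate found nowhere in the documents. A reader might infer that the proportion must reach its ceiling in insulin users and throw away most of the information. The protocol does not support that: 78% against 68% affected is no ceiling, nor is 80% against 75% at a mean of 12 with k = 2, and at 0.1 to 0.3 events almost nothing is lost.

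The window is also unclear. The outcome is given at weeks 12 and 24, whereas steps in the same list have explicit 12-week spans, and the primary outcome treats week 12 as the seven days before the visit. With a one-week window and 0.3 events per week, the powers are 14% and 16%.

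A reader might further infer that the listed test says nothing about the hypothesis, or that a count should replace it. Neither follows. The proportion affected is a common patient-level summary and bears on whether there is less hypoglycemia. Hypoglycemia also enters the primary outcome and the HbA1c composite, and an analysis plan that is not shown could add a rate.

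Nor is a rate free of difficulty. Counting only low meter readings would drop the unconfirmed symptomatic events that the protocol includes, and could count one episode several times. Both summaries depend on how often glucose is measured. Educators telephone ICT-arm patients who stop recording after a feedback message, so measurement may differ by arm. As an illustration with independent readings and an assumed 1% chance each, 84 readings give 1 − 0.99^84 = 57% of patients with an event and 168 give 82%. A follow-up-time offset does not remove this.

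All of this limits the claim and shapes the remedy. It does not remove the mismatch between hypothesis and outcome.

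**Conclusion.** The point holds in conditional form. As written, the hypothesis of fewer events is not tested directly: the only listed between-group comparison of how often hypoglycemia occurs is a yes/no proportion, while event frequency is collected and repeat events are foreseen.

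If patients average about one or more events over the window, much of the information can be lost. Under k = 1 and rate ratio 0.6, the proportion has 11–19% power against 31–56% for the rate at control means of 1 to 12. With k = 2 and a mean of 3.6 it is 11% against 30%. Below about 0.3 events the loss is negligible, so the proportion is adequate for rare types. Rates, dispersion and rate ratio are all assumptions.

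The rate comparison has only modest power under overdispersion, so a null result would still need cautious wording. This is a secondary outcome; the primary outcome and the sample size stand.

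**What to change.** In Outcome variables and Data analysis, add the rate of hypoglycemic episodes (total, asymptomatic, daytime, nocturnal) over weeks 1–12 and weeks 13–24. Use the definitions already in Evaluation of hypoglycemia, including symptomatic events without a confirmed value, and count repeat readings within one episode once.

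Compare the arms with a negative binomial model with log follow-up time as offset, adjusted for the two stratification factors (institution, and pre-prandial insulin two or more times per day). Report it beside the number of self-measurements by arm. Give a per-reading rate as a sensitivity analysis only, because the number of readings arises after randomization and feedback may change it.

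Keep the proportions of patients affected beside the rate, as the main summary for severe hypoglycemia and coma/convulsions, and state the window they cover.

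The cost is one extra model, an overdispersion assumption and a written rule for what makes one episode. No new data collection is needed.

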### ICT-based centralized clinical trial monitoring system

A centralized clinical trial monitoring system based on ICT allows the investigators to store and retrieve personal medical information transmitted from a medical device at an out-of-hospital location (e.g., at home) and to obtain reliable clinical data. This system is expected to be useful for clinical decision making (Fig. 2). The ICT-based centralized clinical trial monitoring system for clinical trials used in this trial consists of 1) a PHR application that acts as a gateway to identify the subjects of the clinical trial and transmit biometric information to the server; 2) at-home measurement device (Bluetooth-enabled blood glucometer); 3) a home monitoring system server where transmitted data is stored, monitored, and transferred; 4) an electronic case report form (eCRF) system (EDC) that extracts and implements the data necessary for clinical trials from the home monitoring system data; and 5) an integrated management server, in which all the above data are collected and managed. The at-home measurement device required for this clinical trial is a blood glucometer linked with Bluetooth, which measures and transmits blood glucose levels to the PHR application with every measurement. Therefore, syncing to the PHR application with Bluetooth is required to save and transmit data to the server automatically. The step count taken per day acquired by the Samsung Health application (Samsung Electronics, Korea) is automatically linked to the PHR application. The Android-based ‘PHR app,’ having recently developed new functions making it capable of interoperability with a wide range of devices, transmission of PHR data to a clinical trial server, and a graphic interface for providing information to medical staff, will be applied for this clinical trial. In addition, subjects can record their insulin protocol, food diary, and ‘hypoglycemia diary’ in the PHR app. The home monitoring system accumulates transferred biometric data, including blood glucose levels measured from the at-home measurement device, step count, and recorded data, including insulin regimen, food diary, and hypoglycemia diary for each registered subject through an integrated management system and transmits the data to the eCRF system via HL7 v2 message, a standardized protocol. For the ICT-based intervention group, PHR app information is sent to the investigator web page in the home monitoring system, and the investigator can view the subject’s data. In addition, algorithm-based feedback messages are transmitted to investigators, as well as subjects in the ICT-based intervention group when blood glucose level is not within the target range. Push feedback messages generated by the home monitoring system server will be displayed on the screen of the subject’s PHR app. eCRF is necessary for inputting and storing clinical trial data for each visit per subject through the integrated management system. Only the investigator or designated person can access the eCRF system to input, store, and examine a subject’s data. The Clinical trial management system (CTMS) is a superordinate system for managing all data, from subject registration and randomization, for transmitting data to the home monitoring system and eCRF and for integrating and managing all data for each measurement per subject. In addition, the CTMS is responsible for the management of participating institutions and investigators, monitoring, and adverse reaction monitoring and reporting. For system data security, the PHR app, the investigator web page, the home monitoring system, the eCRF system, and the integrated CTMS all protect personal medical information and maintain high standards of confidentiality by system log recording methods through automatic logoff, control and authentication on access, data encryption, and data audits.

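### Step counts are compared with no baseline covariate, although the pre-randomisation run-in week could probably supply one; the loss is precision on a secondary outcome, not validity

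*Protocol article*

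**What the plan says.** All places are in the protocol article.

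- **Hypotheses.** The secondary hypothesis expects improvement in "step count, exchange units for each food category, and fewer hypoglycemic events or acute complications relative to the conventional intervention group". The comparison is between arms.
- **Outcome variables.** Steps are defined as "the number of steps taken during weeks" 1–12 and 13–24. No pre-randomisation window is named, and the text does not say whether the summary is a total or a daily mean.
- **Data analysis.** The method is "Student’s t-test or Wilcoxon’s rank-sum test for continuous variables of secondary outcome variables". Comparisons are also to be stratified by institute and by mealtime insulin use. No baseline value of the outcome enters.
- **ICT-based centralized clinical trial monitoring system.** The daily step count from the phone's health application "is automatically linked to the PHR application". The legend to Fig. 1 lists steps among the data sent on to the monitoring servers.
- **Study design; Run-in period; Randomization.** Subjects use the glucometer and the app for one week, with daily synchronisation, and are randomised only if they manage this. The data named for that week do not include steps.

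**The concern.** People differ widely in habitual activity. A two-sample test on follow-up steps leaves all of that spread in the error term. Where the same quantity has been recorded on the same person before allocation, using it as a covariate removes the part of the spread that it predicts, without adding a patient or a visit.

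Here such a measurement probably exists. The app is running before randomisation and steps flow into it without action by the subject. The stated method leaves it unused. At stake is the chance of detecting a real difference in steps in a trial of 96 that was sized for a different, binary outcome.

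**Working it through.** **1. Sample sizes to work with.** The article gives no figure for steps. Its only calculation is for the primary outcome (Sample size assumptions): 55% versus 88%, two-sided 0.05, 90% power. With the pooled-variance formula and no continuity correction, the mean proportion is 0.715 and

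n = [1.960·√(2·0.715·0.285) + 1.282·√(0.55·0.45 + 0.88·0.12)]² / 0.33² = (1.251 + 0.762)² / 0.1089 ≈ 37.2, so 38 per arm.

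Allowing for 20% dropout, 38/0.80 = 47.5, so 48 per arm. Both stated figures reproduce. They say nothing about steps, but they fix the range of usable n: 48 per arm randomised, 38 per arm expected to remain.

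**2. Assumptions, because the documents give no figure.** A true between-arm difference of 0.5 SD in mean daily steps, and a correlation r between run-in and follow-up steps of 0.3, 0.5 or 0.7.

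**3. Effect of adjustment.** ANCOVA multiplies the residual variance by 1 − r². Power for n per arm is approximately

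Φ( 0.5 / √[(1 − r²)·2/n] − 1.96 ).

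For n = 38, √(2/38) = 0.2294:
- r = 0: Φ(2.179 − 1.96) = 0.587
- r = 0.5: Φ(2.179/0.866 − 1.96) = Φ(0.557) = 0.711

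The other entries follow in the same way.

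| r | 1 − r² | Power, 38 per arm | Power, 48 per arm | Detectable difference at 80% power, 38 per arm | Equivalent unadjusted n for 38 |
|---|---|---|---|---|---|
| 0 (as planned) | 1.00 | 59% | 69% | 0.64 SD | 38 |
| 0.3 | 0.91 | 63% | 73% | 0.61 SD | 42 |
| 0.5 | 0.75 | 71% | 81% | 0.56 SD | 51 |
| 0.7 | 0.51 | 86% | 93% | 0.46 SD | 75 |

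The fifth column is (1.960 + 0.842)·√(2/38)·√(1 − r²), and the last is 38/(1 − r²). The arithmetic ignores any further gain from the stratification factors.

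**4. Where the first window starts.** Study design places randomisation during week 1, and the section on telephone counseling places the call that follows the run-in at week 1. A window labelled weeks 1–12 can be read as starting at randomisation or as including some run-in days. Once the run-in is used as baseline, the start needs to be stated so that no day counts twice.

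**The case against.** The case against is substantial, and most of it stands.

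- **A reader might infer that without a baseline the trial cannot show improvement.** The hypothesis is worded relative to the conventional group. Under 1:1 randomisation, a comparison of follow-up steps tests it without bias.
- **A reader might infer that chance imbalance in habitual activity could be mistaken for an effect.** The standard error of a t-test already contains that imbalance, and the 5% error rate covers it.
- **A reader might infer that the food hypothesis is faulty**, because the 3-day diary is kept only "in the breakfast, lunch, and dinner prior to visits 3 and 4". The same reasoning applies: it is a between-arm hypothesis, tested at weeks 12 and 24, and needs no rewording.
- **Run-in steps are inferred, not documented.** The run-in text names only glucose readings, and the instructions in Study design add insulin and the hypoglycemia diary. The study schedule (Table 1) is not visible in the text at hand. Automatic linkage makes capture likely but does not establish it.
- **Covariates are commonly left to an analysis plan, and none is shown.** This has weight. However, the article itself names the tests and the stratification for these outcomes, so the point concerns a stated method.
- **The gain may be small.** One week recorded just after insulin education may predict a 12-week average only weakly. At r = 0.3 the gain with 38 per arm is four percentage points.

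**Conclusion.** The planned analysis of steps is valid but less efficient than it could be. The documents support a loss of precision on one secondary outcome and nothing stronger: no bias, no inflated error rate, no defect in the food-unit comparison and no effect on the primary outcome.

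With 38 per arm and a 0.5 SD difference, the gain in power runs from 4 points (r = 0.3) to 27 points (r = 0.7). With 48 per arm it runs from 4 to 24 points. The effect size and the correlations are assumptions, and the gain also depends on steps having been recorded in the run-in week. This is an optional improvement, worth making because it is cheap.

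**What to change.** 1. Confirm that step counts are transmitted during the run-in week, and state that they are retained.
2. Define the outcome as mean daily steps after randomisation for weeks 1–12 and 13–24, with the first window starting after randomisation.
3. Replace the t-test or rank-sum test for steps with ANCOVA, using run-in mean daily steps and the two stratification factors (institute; mealtime insulin at least twice daily) as covariates.
4. State in advance how partial or absent run-in steps are handled.

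**Cost.** A few sentences of analysis wording, with no added patients, visits or procedures if capture is confirmed. If steps were not captured in that week, the adjustment is not available from existing data and the planned comparison remains valid. Starting to use the app may raise activity slightly during the run-in, but this happens before allocation and does not invalidate the covariate. Food exchange units need no change.
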